4.5 Study protocol and study tools

Upon consent, patients will be enquired regarding their background and the data will be recorded (Appendix III). Information regarding sociodemographic characteristics (smoking history, alcohol consumption and coffee consumption), previous antibiotics use, concomitant medical conditions, current medications and any gastrointestinal symptoms will be recorded. Height and weight are measured and recorded into the data collection sheet. The clinical response to L-dopa will be documented (looking at L-dopa ‘onset’ time (minutes) and L-dopa ‘on-time’ duration (minutes)). The severity of their Parkinson’s disease will be assessed using PDQ-39 questionnaires and the Unified Parkinson’s Disease Rating Scale (UPDRS)-III.

PDQ-39 (Appendix IV)

PDQ-39 is the most widely used disease-specific patient completed rating scale in PD. It consists of 39 questions covering eight aspects of quality of life: mobility, activities of daily living (ADL), emotional well being, social stigma, social support, cognition, communications and bodily discomfort. PDQ-39 has been tested for reliability and validity51. The maximum total score for PDQ-39 is 156 points signifying a poorer quality of life, with subdivisions for mobility (40), ADL (24), emotional well being (24), social stigma (16), social support (12), cognitive impairment (16), communication (12) and bodily discomfort (12).

The Unified Parkinson’s Disease Rating Scale (UPDRS) (Appendix V)

The UPDRS is a rating scale used to assess the severity of PD. It is useful for clinicians as well as researchers to evaluate the progression of the disease and response to treatment. It is comprised of 4 parts. Part I – Mentation, behaviour and mood, Part II – self evaluation of ADLs, Part III – clinician scored motor evaluation and Part IV – Complications of therapy. The first 3 sections (I to III) are rated with a 5-point scale (0 signifying no disability and 4 signifying maximum disability) while the fourth section is used to evaluate patients with more advanced stage who are on treatment. The maximum score for each section is 16, 52, 108 and 23, respectively, giving a total of 199, being the higher the score the greater the disability from PD.

Urea Breath test protocol (Appendix VI)

Each subject undergoes UBT to diagnose H. pylori infection. UBT is selected as the most appropriate tool for diagnosing *H. pylori* in this study because it is noninvasive, non-radiotoxic and readily available compared to OGDS. Serology testing is cheaper and widely accessible and has been used in many researches locally and internationally. Unfortunately, serology testing has a specificity of 79-90% and sensitivity of 76-84%38, 52. Furthermore, patients who are positive for *H. pylori* will remain seropositive for as long as 4 years after its eradication even when UBT has long been negative53.

Subjects who are on PPIs or H2 blockers will be given a later appointment for UBT after 4 weeks of stopping these medications. Each patient will be given 75 mg of IRIS 13C urea mixed in Tang™ Orange juice. Breath sample will be taken at 0 minutes, 10 minutes, 20 minutes and 30 minutes. At each breath, subjects will be asked to inhale deeply and hold for 5 seconds and then blow slowly into a bag until its fully inflated. The breath samples collected will be then analysed using the Non-Dispersive Isotope-Selective InfraRed Spectrometer (NDRIS)[IRIS]. Interpretation of the results are based on the IRIS Software 2.3 for analysis of Delta (δ) over baseline (DOB) (Appendix VII).

Delta over baseline (DOB) APPENDIX VII

Delta (δ) over baseline (DOB) of 13C-urea breath test has been shown to correlate with H. pylori severity infection. It correlates significantly with total urease activity in the stomach and hence a quantitative indicator of *H. pylori* load54, 55. DOB also has been studied extensively and the value shown to be correlated with bacterial strain virulence56, intensity of dyspeptic symptom57 and therapy efficacy58. There is no standard acceptable cutoff for DOB value to divide severity into stages yet. This is because there are many companies with different 13C-UBT protocols with differing 13C-urea dosages and timing of breath collections.

The IRIS Infra Red isotope Analyser quantifies the ratio of 13CO2 with our normal breath 12CO2 in order to measure the current *H. pylori* current infection. DOB value of more than 4.0 is considered *H. pylori* positive while DOB of less than 2.5 is considered negative *H. pylori*. If all the values fall in between the range 2.5 to 4.0, the patient is considered positive if they have taken antibiotics, PPI or H2 antagonist for the last 4 to 6 weeks. Otherwise, patient is considered as negative. The sensitivity and specificity of 13C-UBT is 98.3% and 98.6% repectively with a positive predicted value and negative predicted value of 13C-UBT is 98.2% and 90% respectively35.

Treatment for *H. pylori*

Patients with positive Urea Breath Test (positive for *H. pylori* infection) will be started on eradication therapy of *H. pylori* (oral esomeprazole 40mg twice bd, oral clarithromycin 500mg bd and oral amoxicillin 1000mg bd) for 14 days. This current recommendation was formulated at the Maastricht III Consensus Conference in March 2005 40.

Follow up visit

*H pylori*-infected Parkinsons disease patients will be followed up in the neurology clinic 3 months after eradication therapy of *H pylori*. The clinical response to L-dopa after eradication treatment of *H pylori* will be assessed (looking at L-dopa ‘onset’ time (minutes) and L-dopa ‘on-time’ duration (minutes)). The clinical motor improvement will also be assessed using PDQ-39 questionnaires and the Unified Parkinson’s Disease Rating Scale (UPDRS)-III. Patients will be guided by investigator to answer the all the questionnaires.

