Treatment eradication for *H. pylori* is highly efficacious39. The current recommendation for eradication was formulated at the Maastricht III Consensus Conference in March 2005. Eradication treatment for *H. pylori* consists of a proton pump inhibitor (PPI) oral esomeprazole 40mg twice daily, oral clarithromycin 500mg bd and amoxicillin 1000mg bd (or metronidazole in penicillin allergic patients) for a recommended duration of 7 to 14 days40.

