4.3 Study Flow Chart

*For subject who is on proton pump inhibitor, if there is no contraindication will be withhold for 4 weeks and given a later date for Urea Breath Test

Sample recruitment

Assessment for eligibility

(Fulfillment of Inclusion criteria)

Informed consent

Patient assessment (L-dopa ‘onset’ time and ‘on-time’ duration, UPDRS-III & PDQ39) and data collection

Positive urea breath test (UBT)

Eradication therapy of H.pylori (oral esomeprazole 40mg od, oral clarithromycin 500mg bd and oral amoxicillin 1000mg bd x 14/7)

Assessment of clinical response to L-Dopa (L-dopa ‘onset’ time and ‘on-time’ duration) & clinical motor improvement using UPDRS-III and PDQ-39 Questionnaire

3/12 later

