4.4 Sample size calculation

The sample size iscalculated based on the following formula:

n = 2(sd)2 1 + (r-1)ρ2 _ Pρ2

f(α,β)

diff2 r 1 + (P-1)ρ

= 2 (sd)2

1 – ρ2

f(α,β)

diff2

Note: P = No. of measure before test

r = No. of measure with test

ρ = Correlation between pairs of measurement before and after eradication therapy of *H. pylori*

Ref: Phillips R., Campbell M (1997) Journal Pharmaceutical Statistic 7(2) 215-225

Based on study by Lee WY *et al* in 2008, comparing clinical response to L-dopa before and after *H.pylori* eradication therapy in *H.Pylori* infected PD group, the mean L-dopa ‘onset’ time after *H.Pylori* eradication is 58 minutes (25% improvement from baseline). The calculated number of patients needed in this study is 39 patients. Given the possibility of 10% drop out, a total of 50 patients will be recruited. The power of the study is set at 95% with level of significance of 5%. We will screen a total of 120 patients who were diagnosed Parkinson’s disease using Urea Breath Test (UBT) in order to give us 43 patients with positive UBT. Recruitment of total 50 Parkinson’s patients with H. *pylori* infection positive in this study gives a power of study of 95%.

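### The flow chart (4.3) and the treatment section (4.5) give different esomeprazole doses: 40 mg once daily, and a malformed phrase that most plausibly means 40 mg twice daily

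*Protocol*

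**What the plan says.** Three places in the protocol describe the eradication regimen.

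- **Section 4.3, Study Flow Chart**, at the treatment step for patients with a positive urea breath test: "oral esomeprazole 40mg od, oral clarithromycin 500mg bd and oral amoxicillin 1000mg bd x 14/7".
- **Section 4.5, Treatment for *H. pylori***, for the same patients at the same step: "oral esomeprazole 40mg twice bd, oral clarithromycin 500mg bd and oral amoxicillin 1000mg bd) for 14 days". It then gives a source: "This current recommendation was formulated at the Maastricht III Consensus Conference in March 2005 40", where the final 40 is the reference number.
- **Section 1.2, Treatment**, in the background chapter. It names the same conference and date, "The current recommendation for eradication was formulated at the Maastricht III Consensus Conference in March 2005", and sets out the regimen as "oral esomeprazole 40mg twice daily, oral clarithromycin 500mg bd and amoxicillin 1000mg bd (or metronidazole in penicillin allergic patients". It puts the course length at 7 to 14 days and again cites reference 40.

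Sections 4.3 and 4.5 are both current, operative text. Section 1.2 is background.

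**The concern.** Eradication therapy is the only intervention in this single-group, before-and-after study, and both hypotheses in Chapter 3 concern its effect. The dose of each component should therefore be stated once, or identically wherever it appears. Here the proton pump inhibitor has two frequencies. Staff working from the flow chart would give half the esomeprazole given by staff working from 4.5 read as twice daily. Each could say that they had followed the protocol, and neither dose could cleanly be called a deviation.

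The follow-up assessments listed in 4.3 and 4.5 are the L-dopa response, UPDRS-III and PDQ-39. Neither section lists a repeat breath test, so those assessments would not show directly whether the esomeprazole dose had influenced eradication. That is a further reason to settle on one dose before treatment begins.

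**Working it through.** The protocol states no daily or total esomeprazole dose, so there is no figure of its own to reproduce. The check compares the texts and adds simple dose arithmetic.

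**Inputs.** Unit dose 40 mg (4.3, 4.5 and 1.2). Duration 14 days (4.3 and 4.5). Frequency as each section words it.

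**Formulas.** Daily dose = 40 mg × doses per day. Course total = daily dose × 14 days.

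| Source and reading | Doses per day | Daily dose | Doses in 14 days | Course total |
|---|---|---|---|---|
| 4.3, *od* | 1 | 40 × 1 = 40 mg | 14 | 40 × 14 = 560 mg |
| 4.5, read as *bd* | 2 | 40 × 2 = 80 mg | 28 | 80 × 14 = 1120 mg |
| 4.5, *twice bd* taken literally | 2 × 2 = 4 | 40 × 4 = 160 mg | 56 | 160 × 14 = 2240 mg |

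Section 1.2 gives twice daily, that is 40 × 2 = 80 mg/day, for a course of 7 to 14 days.

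**Can 4.3 and 4.5 be reconciled?** No. Section 4.5 gives 80 or 160 mg/day depending on the reading, and neither equals the 40 mg/day in 4.3. With 4.5 read as *bd*, the ratio is 1120 / 560 = 2.0 and the difference is 28 − 14 = 14 doses per patient.

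**How far does the conflict reach?** Clarithromycin 500 mg *bd*, amoxicillin 1000 mg *bd* and 14 days are the same in 4.3 and 4.5. Only the esomeprazole frequency differs.

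**Which reading does the protocol support?** Section 4.5 ties its regimen to a named conference, a date and reference 40. Section 1.2 names the same conference, date and reference, and gives 40 mg twice daily. The natural explanation of *twice bd* in 4.5 is that *twice* repeats *bd*. Two of the three statements then agree on twice daily, and the flow chart stands alone.

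**The case against.** The strongest reply is that this is a slip in a summary diagram plus one redundant word in 4.5. Section 4.5 is the dedicated treatment text and gives its source, section 1.2 agrees with it, and a careful reader would arrive at twice daily. Because there is one treated group, the discrepancy also cannot unbalance arms. Most of this stands, and it is why the point is minor. It does not remove the point, because no rule of precedence between 4.3 and 4.5 is given and a flow chart is a page that clinic staff can be expected to work from. A reading error in the PDF text is unlikely, since *bd* appears correctly twice on the same line of the flow chart.

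A second objection also stands. The reference list is not available, so the case for twice daily rests on the protocol's own account of the recommendation in 1.2. That supports a likely intent. It does not entitle a statistical reviewer to set a drug dose.

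Some stronger readings are tempting but unsupported:

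- A reader might infer that the L-dopa results would be biased or the study underpowered. The protocol gives no link between esomeprazole dose and outcome, and the sample size and significance level do not depend on it.
- A reader might infer that the whole regimen is undefined. The two antibiotics and the duration agree.
- A reader might infer that 4.5 orders 160 mg/day. That is the literal wording, but 1.2 makes a redundant word far more plausible.
- A reader might multiply up to a trial-wide dose count. Section 4.4 gives both 43 expected positives and 50 recruits, so only the per-patient figure is firm.
- A reader might fold in the penicillin-allergy alternative mentioned in 1.2. Section 1.2 describes a general recommendation, and 4.3 and 4.5 need not adopt every option in it. Its absence there is not part of this contradiction.

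**Conclusion.** The contradiction is real and confined to one component. Section 4.3 gives esomeprazole 40 mg/day and 4.5, on its most plausible reading, 80 mg/day: a two-fold difference in one of three drugs, or 560 mg against 1120 mg over the course. The flow chart is the likely error, and the wording in 4.5 also needs repair.

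This conclusion rests on two assumptions: that *twice* in 4.5 merely duplicates *bd*, and that section 1.2 reports the cited recommendation correctly. If either failed, the intended dose would be less certain, but 4.3 and 4.5 would still disagree. Severity is minor.

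**What to change.** Ask the sponsor's clinical lead to confirm that esomeprazole is meant to be given twice daily. Then:

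1. In 4.3, change *od* to *bd*.
2. In 4.5, change *twice bd* to *bd*.
3. Check that both sections now state the same oral regimen: esomeprazole 40 mg *bd*, clarithromycin 500 mg *bd* and amoxicillin 1000 mg *bd*, for 14 days.
4. Notify the ethics committee of the correction.

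The cost is a wording change in two places. Sample size, visits and analyses are untouched. If drug supply was planned from the flow chart, at most 14 more 40 mg doses per patient are needed; the protocol does not discuss supply, so this is an upper figure.

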4.6 Ethical Consideration

This study will be conducted after the approval of the PPUKM ethics committee. Participants will be explained regarding the procedure and the benefit of the study before they signed the consent form. They are allowed to opt out from the study at any point as they wish.

Appendix I

[figure not shown]

Appendix II

DATA COLLECTION FORM

Subject Initials: Subject #: Date of Visit:

DD MM YR

Paste sticker here Contact Number

A. Checklist:

Parkinson’s Group Control Group

Inclusion Criteria Yes No

1. Diagnosis of idiopathic Parkinson’s disease (PD) by a

neurologist (Hoehn and Yahr Stage I-IV)  

1. Age > 18 and < 90 years old  
2. Written informed consent given either by the patient

or next of kin  

1. Patient on levodopa at least > 1 month  

Exclusion Criteria

1. Patients with a diagnosis of secondary parkinsonism, and

Parkinson’s plus syndrome.  

1. History of recent proton pump inhibitors (PPIs) or histamine (H2)

antagonist use for at least 4 weeks prior to the urea breath test  

1. History of recent antibiotics use (less than 6 months)  
2. Inability to perform Urea Breath Test  

Consent  

|  |
| --- |

UBT date

**Urea Breath Test Result positive**  **negative**

# B. DEMOGRAPHY

**Date of birth Sex**  **Race**

Male Chinese

DD MM YEAR

Female Malay

**Height**: cm Indian

**Weight**: kg Others

_________

**Occupation** :  Professional **Education**  Less than

 Non-professional **level:** primary school

 Unemployed  Secondary School

 Student  University /Colleges

 Master/Postgraduate

and above

**Household Income** < RM 1000

**(per month)** RM 1000-2,500

RM2,500 – 5,000

RM5,000-10,000

>RM10,000

C. PARKINSON’S RISK FACTORS ASSESSMENTS

##

## TOBACCO CONSUMPTION  never

##  occasional

## regular

- ex-smoker

## COFFEE CONSUMPTION  never

##  occasional (<1 cup/day)

 regular (1 cup/day or more)

## ALCOHOL CONSUMPTION  regular drinker__________unit/wk  Non-drinker

## PAST CHEMICAL EXPOSURE  Yes (Details : __________________)

##  No

ANTIBIOTIC USE  Yes (Details : ________________)

- No

FAMILY Hx of:

1. H. Pylori  Yes (Details :_________________)

 No

1. Parkinson’s  Yes (Details _________________)

Disease  No

D. *H. PYLORI* INFECTION ASSESSMENT

## SYMPTOMS: Yes No

## Abdominal pain  

## Heartburn  

## Nausea  vomiting  

Constipation  

## Melena/Hemetemesis  

## Previous OGDS  

## Previous Diagnosis

## with H pylori   If yes:– Eradication details:

Previous Antibiotic Use   Details :

Drug Allergy   Details :

Concomitant Medical Problems and Medications:

1)______________________________________

2)______________________________________

3)______________________________________

E. Parkinson’s Disease Assessment

Age of Diagnosis of Parkinsons years old

Parkinson’s Medications and dose

1. ____________________________________________________
2. ____________________________________________________
3. ____________________________________________________

Appendix III. Motor Fluctuation Parkinson’s Disease Diary

**EFFECTS OF *HELICOBACTER PYLORI* ERADICATION IN PATIENTS WITH PARKINSON’S DISEASE.**

Name: _________________________________________

Contact No: ____________________________________

Thank you very much for participating in this study.

This is a diary to record your motor status for 72 hours.

The diary should be completed by you. Your caregiver can help in filling up the forms. In case you need any help with your diary completion, please contact [name] ([name])

Please tick only one “status” box for each hourly interval on the page and ensure that no hourly interval is left empty

How to select which box to tick:

1. If your medication was providing benefit with regard to mobility, slowness and stiffness, please tick **“ON”** box for that interval
2. If your medication was providing benefit with regard to mobility, slowness and stiffness, but you were experiencing involuntary twisting, turning movements that *did not* interfere with functioning or *did not* cause meaningful discomfort, please tick **“ON with minor (non-troublesome) dyskinesia”** box for that interval
3. If your medication was providing benefit with regard to mobility, slowness and stiffness, but you were experiencing involuntary twisting, turning movements that *interfered* with functioning or *caused* meaningful discomfort, please tick **“ON with troublesome dyskinesia”** box for that interval
4. If your medication had worn off and was no longer providing benefit with regard to mobility, slowness and stiffness, please tick **“OFF”** box for that interval
5. If you were asleep, please tick **“asleep”** box for that interval
6. In the last column, please tick the appropriate boxes and state the time you took your dose of **levodopa**

Note: Dyskinesias are involuntary twisting and turning movements. These movements are an effect of medication and occur during “ON” period. Tremor is shaking back and forth and is NOT considered dyskinesia. Only YOU (patient) can decide whether the dyskinesia is troublesome or minor.

| **DAY ONE DATE:** | | | | | | |
| --- | --- | --- | --- | --- | --- | --- |
| **Time** | **ON** | **ON with minor dyskinesia** | **ON with troublesome dyskinesia** | **OFF** | **Asleep** | **Levodopa Intake (state exact time)** |
| **0600-0700** |  |  |  |  |  |  |
| **0700-0800** |  |  |  |  |  |  |
| **0800-0900** |  |  |  |  |  |  |
| **0900-1000** |  |  |  |  |  |  |
| **1000-1100** |  |  |  |  |  |  |
| **1100-1200** |  |  |  |  |  |  |
| **1200-1300** |  |  |  |  |  |  |
| **1300-1400** |  |  |  |  |  |  |
| **1400-1500** |  |  |  |  |  |  |
| **1500-1600** |  |  |  |  |  |  |
| **1600-1700** |  |  |  |  |  |  |
| **1700-1800** |  |  |  |  |  |  |
| **1800-1900** |  |  |  |  |  |  |
| **1900-2000** |  |  |  |  |  |  |
| **2000-2100** |  |  |  |  |  |  |
| **2100-2200** |  |  |  |  |  |  |
| **2200-2300** |  |  |  |  |  |  |
| **2300-0000** |  |  |  |  |  |  |
| **0000-0100** |  |  |  |  |  |  |
| **0100-0200** |  |  |  |  |  |  |
| **0200-0300** |  |  |  |  |  |  |
| **0300-0400** |  |  |  |  |  |  |
| **0400-0500** |  |  |  |  |  |  |
| **0500-0600** |  |  |  |  |  |  |

| **DAY TWO DATE:** | | | | | | |
| --- | --- | --- | --- | --- | --- | --- |
| **Time** | **ON** | **ON with minor dyskinesia** | **ON with troublesome dyskinesia** | **OFF** | **Asleep** | **Levodopa Intake (state exact time)** |
| **0600-0700** |  |  |  |  |  |  |
| **0700-0800** |  |  |  |  |  |  |
| **0800-0900** |  |  |  |  |  |  |
| **0900-1000** |  |  |  |  |  |  |
| **1000-1100** |  |  |  |  |  |  |
| **1100-1200** |  |  |  |  |  |  |
| **1200-1300** |  |  |  |  |  |  |
| **1300-1400** |  |  |  |  |  |  |
| **1400-1500** |  |  |  |  |  |  |
| **1500-1600** |  |  |  |  |  |  |
| **1600-1700** |  |  |  |  |  |  |
| **1700-1800** |  |  |  |  |  |  |
| **1800-1900** |  |  |  |  |  |  |
| **1900-2000** |  |  |  |  |  |  |
| **2000-2100** |  |  |  |  |  |  |
| **2100-2200** |  |  |  |  |  |  |
| **2200-2300** |  |  |  |  |  |  |
| **2300-0000** |  |  |  |  |  |  |
| **0000-0100** |  |  |  |  |  |  |
| **0100-0200** |  |  |  |  |  |  |
| **0200-0300** |  |  |  |  |  |  |
| **0300-0400** |  |  |  |  |  |  |
| **0400-0500** |  |  |  |  |  |  |
| **0500-0600** |  |  |  |  |  |  |

| **DAY THREE DATE:** | | | | | | |
| --- | --- | --- | --- | --- | --- | --- |
| **Time** | **ON** | **ON with minor dyskinesia** | **ON with troublesome dyskinesia** | **OFF** | **Asleep** | **Levodopa Intake (state exact time)** |
| **0600-0700** |  |  |  |  |  |  |
| **0700-0800** |  |  |  |  |  |  |
| **0800-0900** |  |  |  |  |  |  |
| **0900-1000** |  |  |  |  |  |  |
| **1000-1100** |  |  |  |  |  |  |
| **1100-1200** |  |  |  |  |  |  |
| **1200-1300** |  |  |  |  |  |  |
| **1300-1400** |  |  |  |  |  |  |
| **1400-1500** |  |  |  |  |  |  |
| **1500-1600** |  |  |  |  |  |  |
| **1600-1700** |  |  |  |  |  |  |
| **1700-1800** |  |  |  |  |  |  |
| **1800-1900** |  |  |  |  |  |  |
| **1900-2000** |  |  |  |  |  |  |
| **2000-2100** |  |  |  |  |  |  |
| **2100-2200** |  |  |  |  |  |  |
| **2200-2300** |  |  |  |  |  |  |
| **2300-0000** |  |  |  |  |  |  |
| **0000-0100** |  |  |  |  |  |  |
| **0100-0200** |  |  |  |  |  |  |
| **0200-0300** |  |  |  |  |  |  |
| **0300-0400** |  |  |  |  |  |  |
| **0400-0500** |  |  |  |  |  |  |
| **0500-0600** |  |  |  |  |  |  |

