**Study Objectives**

Primary Objectives:

- To compare the clinical response to L-dopa before and after *H. pylori* eradication therapy in the *H. pylori* infected PD group. (L-dopa ‘onset’ time (minutes) and L-dopa ‘on-time’ duration (minutes) ).

Secondary Objectives:

- To assess clinical motor improvement before and after *H. pylori* eradication therapy in infected PD group, using the UPDRS-III and PDQ39 questionnaires.

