Appendix III(c).

**KESAN PEMBASMIAN JANGKITAN *HELICOBACTER PYLORI* DI KALANGAN PESAKIT PARKINSON**

姓名: _________________________________________

电话号码: ____________________________________

谢谢您参与这次的研究。

这是一本记录您72小时运动机能的日记。

您需要亲自完成日记。您的护理员可以帮助您填写表格。

请在每半小时的间隔中只在日记页的一个“状态”空格内画勾并且确保完成了所有的一小时间隔。

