**如何选择在什么空格里画勾**

1. 如果您的药物治疗对治疗灵动性，迟缓和僵硬有益，请在这半小时间隔的“**起效**”空格中画勾。
2. 如果您的药物治疗对治疗灵动性，迟缓和僵硬有益，但是您在体会不影响身体功能或不会引起重大的不适的偶然的扭曲，旋转运动，请在这半小时间隔的**“伴有轻微的（非棘手运动障碍）”**空格中画勾。
3. 如果您的药物治疗对治疗灵动性，迟缓和僵硬有益, 但是您在体会到影响身体功能或引起重大的不适的偶然的扭曲，旋转运动，请在这半小时间隔的**“伴有运动障碍”**空格中画勾。
4. 如果您的药物治疗效果减弱不再对治疗灵动性，迟缓和僵硬有益, 请在这半小时间隔的**“失效”**空格中画勾。
5. 如果您在熟睡中，请在这半小时间隔的**“熟睡”**空格中画勾。
6. 在最后的竖排中，请在合适的空格勾出您服用levodopa的时间。

注意：运动障碍是偶然的扭曲，旋转运动。这些运动不是药物的效用并且出现在起效时间内。颤动是来回地颤动并且不被认定为运动障碍。

只有您本人（患者）可以决定在任何的半小时时间中出现的运动障碍（偶然的扭曲，旋转运动）是棘手的还是轻微的（不棘手的）。

| **第 一 天 日期 ：** | | | | | | |
| --- | --- | --- | --- | --- | --- | --- |
| **时间** | **起效** | **非棘手**  **运动障碍** | **伴有**  **运动障碍** | **失效** | **熟睡** | **使用 Levodopa**  **写时间** |
| **0600-0700** |  |  |  |  |  |  |
| **0700-0800** |  |  |  |  |  |  |
| **0800-0900** |  |  |  |  |  |  |
| **0900-1000** |  |  |  |  |  |  |
| **1000-1100** |  |  |  |  |  |  |
| **1100-1200** |  |  |  |  |  |  |
| **1200-1300** |  |  |  |  |  |  |
| **1300-1400** |  |  |  |  |  |  |
| **1400-1500** |  |  |  |  |  |  |
| **1500-1600** |  |  |  |  |  |  |
| **1600-1700** |  |  |  |  |  |  |
| **1700-1800** |  |  |  |  |  |  |
| **1800-1900** |  |  |  |  |  |  |
| **1900-2000** |  |  |  |  |  |  |
| **2000-2100** |  |  |  |  |  |  |
| **2100-2200** |  |  |  |  |  |  |
| **2200-2300** |  |  |  |  |  |  |
| **2300-0000** |  |  |  |  |  |  |
| **0000-0100** |  |  |  |  |  |  |
| **0100-0200** |  |  |  |  |  |  |
| **0200-0300** |  |  |  |  |  |  |
| **0300-0400** |  |  |  |  |  |  |
| **0400-0500** |  |  |  |  |  |  |
| **0500-0600** |  |  |  |  |  |  |

| **第 二 天 日期 ：** | | | | | | |
| --- | --- | --- | --- | --- | --- | --- |
| **时间** | **起效** | **非棘手**  **运动障碍** | **伴有**  **运动障碍** | **失效** | **熟睡** | **使用 Levodopa**  **写时间** |
| **0600-0700** |  |  |  |  |  |  |
| **0700-0800** |  |  |  |  |  |  |
| **0800-0900** |  |  |  |  |  |  |
| **0900-1000** |  |  |  |  |  |  |
| **1000-1100** |  |  |  |  |  |  |
| **1100-1200** |  |  |  |  |  |  |
| **1200-1300** |  |  |  |  |  |  |
| **1300-1400** |  |  |  |  |  |  |
| **1400-1500** |  |  |  |  |  |  |
| **1500-1600** |  |  |  |  |  |  |
| **1600-1700** |  |  |  |  |  |  |
| **1700-1800** |  |  |  |  |  |  |
| **1800-1900** |  |  |  |  |  |  |
| **1900-2000** |  |  |  |  |  |  |
| **2000-2100** |  |  |  |  |  |  |
| **2100-2200** |  |  |  |  |  |  |
| **2200-2300** |  |  |  |  |  |  |
| **2300-0000** |  |  |  |  |  |  |
| **0000-0100** |  |  |  |  |  |  |
| **0100-0200** |  |  |  |  |  |  |
| **0200-0300** |  |  |  |  |  |  |

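### Both primary endpoints are in minutes and the planned onset change is about 19 minutes, but the only ON/OFF form shown is an hourly-box diary that the methods never name as the source, and its Chinese version does not match its own grid

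*Protocol*

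**What the plan says.** Study Objectives (Chapter 2) sets the primary endpoints as "L-dopa ‘onset’ time (minutes) and L-dopa ‘on-time’ duration (minutes"). Section 4.5 repeats these units for the baseline and the three-month assessment. It says only that the response is documented or assessed, and names no instrument. Its one mention of Appendix III concerns background data.

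Section 4.4 bases the sample size on onset time. The mean after eradication "is 58 minutes (25% improvement from baseline"). The calculated number is 39, with 50 to be recruited for 10% dropout, power 95% and significance level 5%. The formula uses an SD and a before-after correlation, but neither value is given.

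Appendix III is a 72-hour diary with hourly rows. The patient ticks one status "box for each hourly interval on the page and ensure that no hourly interval is left empty". Only levodopa intake is recorded as an exact time.

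The three language versions differ:
- **Interval.** English and Malay are hourly throughout. The Chinese version opens with "请在每半小时的间隔中只在日记页的一个", an instruction to tick one box per half hour. The same sentence ends by asking for all one-hour intervals to be completed, and items 1–5 again refer to half hours. The printed grid is hourly.
- **Dyskinesia note.** The English reads "These movements are an effect of medication and occur during" the ON period, and the Malay agrees. The Chinese reads "这些运动不是药物的效用并且出现在起效时间内", which says the movements are not an effect of medication.
- **Levodopa time.** The English and Malay column heads ask for the exact time. The Chinese head asks for the time only.

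**The concern.** The planned onset change is about a third of one diary row. If onset and on-time are read from the diary, each reading is rounded to a whole box, and the patient decides unaided how to mark an hour in which the state changed. The same true improvement can then be recorded as nothing or as a full hour, depending on when the dose falls within the hour and on the patient's ticking habit. An analysis plan written later cannot recover minutes that were never recorded, so this belongs to the form and the methods text. Inconsistent instructions in one language add avoidable variation between patients in how the same form is completed.

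**Working it through.** **Planned effect (derived; the protocol does not print it).** Baseline = 58/0.75 = 77.3 min. Change = 77.3 − 58 = 19.3 min. That is 19.3/60 = 32% of an hourly box, or 64% of a half-hour box.

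**The plan's own figure.** The formula in section 4.4 reduces to n = 2·SD²·(1−ρ²)·f/diff². With two-sided 5% and 95% power, f = 12.99 (sidedness is not stated). SD and ρ are missing, so 39 cannot be reproduced. Solving backwards, SD·√(1−ρ²) = √(39 × 19.33²/(2 × 12.99)) = 23.7 min. The SD of change is SD·√(2(1−ρ)):
- ρ = 0: SD = 23.7, SD of change = 33.5 min
- ρ = 0.7: SD = 33.2, SD of change = 25.7 min

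The range of ρ is an assumption.

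**What one reading looks like.** Take the recorded onset as the start of the first ON box minus the dose time, and tick by the state in most of the hour.
- Dose 08:00: true onsets at 09:17 and 08:58 both give first ON box 09–10. Recorded 60 and 60 min; change 0.
- Dose 08:30: true onsets at 09:47 and 09:28 give first ON boxes 10–11 and 09–10. Recorded 90 and 30 min; change 60.
- Dose 08:00, but a box is ticked ON if any part of it was ON: recorded 60 and 0 min; change 60.

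**Mean recorded change for a true 19.3 min (simulation; three tick rules: majority of the hour, any ON, state at the end of the hour).**

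| Dose timing | Within-patient SD of onset | 60-min boxes |
| --- | --- | --- |
| On the hour or half hour | near 0 | 0 or 60 |
| On the hour or half hour | 10 min | 6 to 32 |
| On the hour or half hour | 20–30 min | about 17 to 22 |
| Spread evenly over the hour | 0–30 min | about 19 |

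Bias therefore needs both clock-aligned doses and small dose-to-dose variation. Otherwise the grid only adds noise.

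**Worst-case loss of power.** Assume one fixed rounding error per patient per visit, independent between visits, and a planning SD free of measurement error. Rounding SD = 60/√12 = 17.3 min (30/√12 = 8.7 min for half-hour boxes). SD of change with rounding = √(SD² + 2 × rounding SD²). For the 60-min grid this gives √(33.5² + 2 × 17.3²) = 41.5 and √(25.7² + 2 × 17.3²) = 35.5 min. Two-sided paired t-test, change 19.33 min:

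| | ρ = 0 | ρ = 0.7 |
| --- | --- | --- |
| No rounding, n = 39 | 94% | 99.6% |
| 60-min grid, n = 39 | 81% | 91% |
| 30-min grid, n = 39 | 91% | 98.5% |
| 60-min grid, n = 45 (50 less 10%) | 86% | 95% |

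A simulation of 800 runs with the majority rule and no dose-to-dose variation gave 79–88% at n = 39, in line with the formula. With 10 min of variation over nine doses, power at the lower end falls only from about 94% to 90–92%.

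**Other forms shown.** UPDRS Part III records one ON/OFF state and minutes since the last medication. UPDRS item 39 records the share of the waking day spent off in broad bands. Neither yields onset or duration in minutes.

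**The case against.** The strongest reply is that nothing in the protocol ties the diary to the primary endpoints. Onset and on-time could be taken by observation or interview in clinic, and Appendices VI and IX are figures not reproduced here. That stands. A reader might infer that the diary is the only instrument and that the endpoints must come from it. The documents show only that it is the one visible form able to supply them. The supported defect is that the source is unnamed, and that the form on hand is coarse if it is the source.

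Second, the hypothesis concerns a group mean, not one patient's reading. Averaging over doses, days and patients recovers most of the shift unless dosing is clock-aligned and responses are regular. Section 1.3 itself describes erratic response to levodopa, with irregular delivery to the brain being common in PD. This stands too, so hourly boxes do not make the planned effect undetectable.

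Third, the Chinese form might be read as impossible to follow or as producing unusable data. The text does not go that far. The sentence that opens with half hours also asks for all one-hour intervals, the grid offers only hourly rows, and the column head asks for a time. The dyskinesia error cannot alter onset or total on-time, because every dyskinesia column is an ON column and the Chinese note still places these movements within ON time. The share of patients using this version is unknown. The contradictions remain and should be corrected, but no effect on the primary result can be claimed.

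**Conclusion.** The concern holds in conditional form. The mismatch of scale is certain: endpoints in minutes, a planned onset change of 19.3 min, and the only visible time-course form in 60-minute rows without a tick rule or a stated link to the endpoints. Its cost depends on the diary being the source.

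Given that, the worst case is power of about 81–91% at 39 patients, or 86–95% at 45 completers, against the stated 95%. This rests on one fixed rounding error per visit and on an SD and correlation inferred backwards from n = 39. With dose times spread over the hour, or about 10 min of variation between doses, the loss is a few points. With clock-aligned dosing and little variation the recorded mean change can be biased (6 to 32 min at a within-patient SD of 10 min), which more patients would not cure. None of these figures covers on-time duration, for which section 4.4 states no planned effect.

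The Chinese version's discrepancies in interval, dyskinesia note and levodopa time are errors whatever the power argument.

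**What to change.** 1. In section 4.5, name the diary as the source of onset time and on-time duration, and state how each is derived. If another instrument is intended, name that one instead.
2. Add two clock-time entries per dose beside the existing levodopa-time column: the time the patient turned ON and the time the effect wore off. Derive both endpoints from these. At the least, use a 30-minute grid with a stated rule for a change of state within an interval.
3. Make the three language versions agree. The Chinese instructions should use the interval of the printed grid, carry the same dyskinesia note as the English and Malay, and ask for the exact levodopa time.

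The cost is a form revision and a check of the translations before first use, plus slightly more patient effort over 72 hours at each of the two assessments.
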